### 2.7. Evaluation Criteria for TCM Syndrome Effect

Statistics are carried out according to the improvement of clinical symptom score with reference to the *Guidelines for Clinical Research of Chinese Medicine (New Drug)* [38], and the primary and secondary symptoms of spleen-kidney qi deficiency and toxicity stasis inter-combination syndrome will be classified as mild, moderate, and severe with 4, 8, and 12 points and 2, 4, and 8 points, respectively. The two total scores calculated by the measurement scale according to TCM symptoms for each patient will be summed up, and then, they will be used to calculate efficacy indicator (EI):  EI = (total symptom score before treatment -total symptom score after treatment)/total symptom score before treatment *X* 100%  EI is adopted to evaluate the treatment efficacy after treatment. Symptom improvement levels will be demonstrated in following categories: clinical control (EI ≥ 95%), significant effect (94% > EI ≥ 70%), and effectiveness (69% > EI ≥ 30%) to inefficacy (EI < 30%).

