#### 2.3.3. Diagnostic Criteria for TCM Syndrome Differentiation

According to Guidelines for Clinical Research of Chinese Medicine (New Drug) [38] and Diagnosis, Syndrome Differentiation, and Efficacy Evaluation of Chronic Renal Failure (Trial Protocol) [39], patients conformed to 4 primary symptoms and 1–2 secondary symptoms listed below can be diagnosed with spleen-kidney qi deficiency and toxicity stasis inter-combination syndrome. The primary symptoms are as follows: (1) fatigue or shortness of breath and reluctance to speak; (2) nausea and vomiting; (3) dim complexion; and (4) soreness in waists and knees. The secondary symptoms are as follows: (1) abdominal fullness and distention; (2) lack of appetite and numb to react; (3) squamous and dry skin; (4) thick and greasy tongue coating; (5) dark and purple tongue or petechiae; and (6) fine tart or slow sunken pulse.

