### 2.6. Outcome Measures

The primary evaluation outcome will be the change in the slope of Scr over 2 weeks. Posttreatment changes in BUN, eGFR, and urinary AKI biomarkers including urinary NGAL, IL-18, *γ*-GT, and TCM symptoms will be the secondary evaluation outcomes.

In addition to the secondary evaluation outcome, inflammatory indicators including TNF-*α* and IL-6 and oxidative stress indicators including heme oxygenase-1 (HO-1), malondialdehyde (MDA), and superoxide dismutase (SOD) will also be measured before and after treatment.

Safety outcomes and vital sign indicators (electrocardiogram, blood routine, urine routine, serum potassium, hemoglobin, etc.) will be recorded once before and 2 weeks after medication. Meanwhile, AEs will be closely observed, meticulously recorded, and properly handled by investigators throughout the study.

HCG: human chorionic gonadotropin; Scr: serum creatinine; BUN: blood urea nitrogen; eGFR: estimated glomerular filtration rate; TCM: traditional Chinese medicine; NGAL: neutrophil gelatinase-associated lipocalin: IL-18: interleukin-18; *γ*-GT: gamma-glutamyl transpeptidase; IL-6: interleukin-6; TNF-*α*: tumor necrosis factor-*α*; HO-1: heme oxygenase-1; MDA: malondialdehyde; SOD: superoxide dismutase.

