### 2.10. Statistical Analysis

The principal analysis will be conducted on a full analysis set (FAS), which consists of participants randomly allocated into two groups. Participants completing and complying well with the study protocol without major violation will be referred to the per-protocol population. All participants taking test drugs will be enrolled in safety analysis and conform with the ITT principle.

For non-normally distributed variables, mean ± standard deviation or median will be brought to describe continuous variables. Categorical variables will be presented in the form of numbers and percentages. The difference in Scr will be tested using the one-way ANOVA with repeated measures. The secondary outcomes will be compared between two groups using the independent-samples Student's *t*-tests for normally distributed continuous data and using Pearson's chi-square test (or Fisher's exact test if cell count <5 in any cell) for categorical data. Two-sided tests will be used for all statistical tests, and *P* < 0.05 will be considered statistically significant. SPSS (version 21.0) software will be used to carry out statistical analysis by a biostatistician not involved in the study. No additional analyses or interim analysis will be performed.

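### The TCM symptom outcome is judged on percent change and its classes with no baseline-adjusted comparison, and the protocol does not say which of the two is tested

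*Protocol article*

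**What the plan says.** Section 2.6 lists post-treatment changes in several measures and ends that list with the statement that "TCM symptoms will be the secondary evaluation outcomes".

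Section 2.7 grades each primary and secondary symptom, "classified as mild, moderate, and severe with 4, 8, and 12 points and 2, 4, and 8 points, respectively", sums the points, and defines "EI = (total symptom score before treatment -total symptom score after treatment)/total symptom score before treatment", expressed as a percentage. It then says that "EI is adopted to evaluate the treatment efficacy after treatment" and presents improvement in four levels: "clinical control (EI ≥ 95%), significant effect (94% > EI ≥ 70%), and effectiveness (69% > EI ≥ 30%) to inefficacy (EI < 30" per cent).

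Section 2.10 compares secondary outcomes by independent-samples t-test when they are continuous and normally distributed, and by "Pearson's chi-square test (or Fisher's exact test if cell count <5 in any cell) for categorical data". It names no baseline covariate. Table 3 schedules TCM symptoms at baseline and at week 2.

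**The concern.** Two features of the measure deserve attention. EI has the baseline score in its denominator, so the same fall in points earns a different EI, and possibly a different class, according to how ill the patient was at entry. Cutting EI into four classes then discards most of the detail in a score that can take many values.

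The other secondary outcomes listed in section 2.6 are laboratory values. The EI classes are the only categorical form the article gives to a secondary outcome, so a reader may well take the chi-square test to be meant for them. The article does not say so.

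At stake is the chance of detecting a real difference in symptoms, and the ease of reading the result. Randomisation is simple, with no severity stratum stated, and no test in section 2.10 adjusts for a chance difference in baseline severity.

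**Working it through.** **Plan's own figures.** No mean, SD, effect or power is given for the TCM score. The only sample size is for serum creatinine: 54 per group after 20% dropout. A three-group F-test with SD 44.43, one mean 30 lower, alpha 0.05 and power 0.90 needs 43 per group; 43/0.80 = 53.75, so 54 per group and 162 in all. Hence about 43 evaluable per arm for the TCM outcome too.

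**Range of the baseline score.** Section 2.3.3 says that "patients conformed to 4 primary symptoms and 1–2 secondary symptoms listed below can be diagnosed". With the section 2.7 points:
- lowest: 4×4 + 1×2 = 18
- highest with two secondary symptoms: 4×12 + 2×8 = 64 (4×12 + 6×8 = 96 if all six secondary symptoms could score)

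**EI for a fixed fall.** Take 8 points, one grade in two primary symptoms, assuming that an absent symptom scores 0.

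| Baseline | EI | Class |
|---|---|---|
| 18 | 8/18 = 44.4% | effectiveness |
| 26 | 8/26 = 30.8% | effectiveness |
| 34 | 8/34 = 23.5% | inefficacy |
| 64 | 8/64 = 12.5% | inefficacy |

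The switch comes at 8/0.30 = 26.7 points. A baseline of 34 is four moderate primary symptoms and one mild secondary one (4×8 + 2).

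**Power, simulation A.** All TCM inputs are assumed: two arms of 43 or 54, baseline mean 40, SD 8 or 12, baseline-to-final correlation 0.3, 0.5 or 0.7, mean comparator fall 14, two-sided 0.05, class cut-offs closed at 30/70/95, 1,500 runs for each of 24 scenarios. The effect was set to SD × √(1−ρ²) × 3.2415 × √(2/n), which gives ANCOVA about 90% by design; the gaps are what matter. Example: SD 12, ρ 0.5, n 43 gives 12 × 0.866 × 3.2415 × 0.2157 = 7.3 points.

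| Analysis | Example (additive) | Range over scenarios |
|---|---|---|
| ANCOVA, total score | 0.90 | 0.87-0.90 |
| t-test, continuous EI | 0.87 | 0.78-0.89 |
| t-test, change score | 0.77 | 0.71-0.85 |
| rank test, four classes | 0.80 | 0.64-0.80 |
| chi-square, four classes | 0.62 | 0.53-0.63 |

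Within scenarios, the shortfall from ANCOVA was 25.8-34.5 points for chi-square on the classes, 9.2-23.2 for the rank test and 1.2-10.0 for continuous EI. The proportional scenarios here kept a constant scatter in points.

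**Power, simulation B.** A second set, also on assumed inputs, contrasted relief as a number of points with relief as a fraction of baseline. ANCOVA had 86-90%, chi-square on the classes 49-65% and the rank test 67-78%. The t-test on continuous EI was 6-14 points below ANCOVA under additive relief and 1-3 points above it under proportional relief.

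Both sets rank the class tests below ANCOVA under either form of relief. The place of continuous EI depends on the form of relief and of its scatter.

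**The case against.** The strongest reply is that section 2.7 adopts EI, a continuous percentage, and that the four levels may be for display only. Section 2.10 has a t-test for continuous outcomes, so the classes need never be tested. This stands: the text does not settle it, and the large power losses apply only if the classes are tested.

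Second, percent relief may be the intended scale. Losing 8 of 18 points and 8 of 64 are different proportional reliefs. Points are not a perfect yardstick either: a secondary symptom loses 4 points from severe to moderate and 2 from moderate to mild. So a reader might infer that section 2.7 misclassifies patients with identical relief, but that presumes the point scale is the right one. The arithmetic shows only that the class for a given point fall depends on baseline. Nor does EI always cost power, since under proportional relief it can do slightly better.

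Third, a reader might see a contradiction between sections 2.6 and 2.7. There is none: EI is a post-treatment change, expressed relative to baseline.

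Fourth, chance imbalance is not a validity flaw. Under no effect, in a separate simulation of two-arm trials with graded symptoms, the chi-square and rank tests on the classes and ANCOVA rejected in 3.4-5.4% of trials. Adjustment is worth having for precision, not to rescue the error rate.

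Finally, covariate choice is often left to an analysis plan. But section 2.10 does fix the tests for secondary outcomes, and as fixed they are unadjusted. A score-change comparison, which section 2.6 does not exclude, would be an unadjusted t-test as well.

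**Conclusion.** The point holds as an improvement to a secondary outcome, not as an error that invalidates the trial. The exact part is the arithmetic: on the protocol's own points and cut-offs, 8 points off is EI 44.4% at baseline 18 and 12.5% at 64.

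The power part rests on assumed means, SDs, correlations and effects, because the protocol gives none for this score. If the classes are tested, the ends of the simulation B ranges put the loss against ANCOVA at 86−65 = 21 to 90−49 = 41 points for chi-square and 86−78 = 8 to 90−67 = 23 for a rank test. An ordered test alone therefore does not recover the loss. If continuous EI is tested, the loss was up to about 14 points under additive relief, and nil or slightly reversed under proportional relief. The additive figure grows when baseline scores are widely spread relative to the scatter in relief, so it is not a bound.

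The recommendation is sound whichever of EI or its classes was meant. The primary analysis and the sample size of 162 are unaffected.

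**What to change.** In sections 2.7 and 2.10, state that the inferential TCM comparison is the total symptom score at week 2, compared between arms by ANCOVA with the baseline total score as covariate, and reported as the adjusted mean difference with 95% CI. State that EI and its four classes are given as a descriptive table and are not tested.

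The cost is about two sentences. Table 3 already has TCM symptoms at both time points, so no patient, visit or measurement is added. There are two downsides: the customary EI classes lose their inferential role, and a point or so of power (1-3 in the simulations) may be given up if relief is truly proportional.

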### 2.8. Data Entry and Management

Case report forms (CRFs) will be filled out by investigators, and each selected participant must complete CRFs. All information in CRFs should be accurately and truthfully recorded. Completed CRFs will be inspected by the clinical supervisor, and then, they should be delivered to the data administrators. Data entry and management will be accomplished by designated data administrators. Patients' personal information should be kept strictly confidential. All date should be recognized through coding numbers without displaying their personal information directly. All date will not be accessible without the permission of the supervisor. The data administrator will use EpiData software to compile data entry software and carry out data entry and management. The supervisor will be in charge of data entry and management procedure. As GCP requires, all date is required to keep for at least five years in the database after the trial accomplishes.

### 2.9. Sample Size Estimation

The sample size will be calculated according to the primary outcome of baseline Scr change. Based on previous studies and literature reports [26, 30], the mean value of Scr was 160.39 *μ*mol/l, and the standard deviation was 44.43 *μ*mol/l. We thus hypothesize that Scr for CHF combing RG group would be significantly lower than the other two groups by more than 30 *μ*mol/l. It is calculated using the sample size estimation software PASS (version 15.0.3) to achieve test efficacy 1–*β* = 0.90 and significant difference *α* = 0.05 (one-sided test). Considering 20% drop rate, the estimated sample size for randomization will be 54 cases in each group for a total of 162 cases.

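### The sample size uses the SD of a serum creatinine level for a change outcome, so the stated 90% power is supported only if the baseline to week-2 correlation is about 0.5 or higher

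*Protocol article*

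**What the plan says.** Three sections of the protocol article bear on this.

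- **2.6 Outcome Measures:** "The primary evaluation outcome will be the change in the slope of Scr over 2 weeks".
- **2.9 Sample Size Estimation:** the sized quantity is named as a change ("The sample size will be calculated according to the primary outcome of baseline Scr change"). The inputs are then given as "the mean value of Scr was 160.39 *μ*mol/l, and the standard deviation was 44.43 *μ*mol/l", and the effect as "Scr for CHF combing RG group would be significantly lower than the other two groups by more than 30 *μ*mol/l". Target power is 0.90 at α = 0.05. The result is printed as "Considering 20% drop rate, the estimated sample size for randomization will be 54 cases in each group for a total of 162 cases".
- **Analysis section (2.10):** creatinine is to be tested by a repeated-measures ANOVA. No baseline covariate is mentioned.

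Table 3 schedules creatinine at week 0 and week 2 only. No section gives an SD of the change or a within-patient correlation.

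**The concern.** A mean of 160.39 μmol/l cannot be a 2-week change when the hypothesised group difference is 30. The SD of 44.43 printed beside it is therefore the spread of creatinine between patients at one time point. The spread of a within-patient change is a different quantity. It depends on how strongly the two measurements correlate, and the article is silent on that.

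At stake is whether the stated 90% applies to the outcome the trial will report. If the change varies more than the level does, the trial has less power than claimed. If it varies less, more patients are randomised than the stated target requires.

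**Working it through.** **Inputs.** From 2.9: SD 44.43, difference 30, α = 0.05, power 0.90, dropout 20%, three equal groups. The correlation r is not in the document, so a range is assumed.

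**Step 1: reproduce the printed size.** Take group means 160.39, 160.39 and 130.39. The squared deviations from their average are 10² + 10² + 20² = 600. For the one-way F test with n per group, the noncentrality is λ = n × 600 / SD².

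- n = 43: λ = 25800 / 44.43² = 13.07, with 2 and 126 degrees of freedom; power is 0.903.
- n = 42: power is 0.895, so 43 is the smallest adequate number.
- Dropout: 43 / 0.80 = 53.75, rounded up to 54; 3 × 54 = 162.

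This matches 2.9. Two-group calculations do not. The normal approximation gives 38 per group one-sided (48 after dropout) or 47 two-sided (59). The exact t test gives 39 (49) or 48 (60). Section 2.9 does not name the test, so the three-group F test is inferred from this match.

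**Step 2: what the planned analysis tests.** With two visits, a slope over 2 weeks is the week-2 minus baseline difference divided by a constant, and that constant does not affect power. The group-by-time test of a two-visit repeated-measures ANOVA is equivalent to a one-way ANOVA on the raw change. Section 2.5 speaks of weekly examinations, but Table 3 marks no week-1 creatinine. Even with one, the least-squares slope through three equally spaced points uses only the first and last.

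**Step 3: power for the raw change.** With equal SDs at both visits, SD of change = 44.43 × √(2(1 − r)). Example at r = 0.3: 44.43 × √1.4 = 52.57; λ = 25800 / 52.57² = 9.34; power is 0.776.

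| Assumed r | SD of change | F-test power, 43 per group | Total randomised for 90% |
|---|---|---|---|
| 0.2 | 56.2 | 72% | 255 |
| 0.3 | 52.6 | 78% | 225 |
| 0.4 | 48.7 | 84% | 192 |
| 0.5 | 44.4 | 90% | 162 |
| 0.6 | 39.7 | 96% | 132 |
| 0.7 | 34.4 | 99% | 102 |

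The exact break-even for the F test with 43 per group is r = 0.496.

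**Step 4: how firm is the 0.5?** If the week-2 SD is k times the baseline SD of 44.43, the change has SD 44.43 when r = k/2. That is 0.4 for k = 0.8 and 0.6 for k = 1.2. For a single pairwise t test with 43 per group, break-even is 0.44 one-sided and 0.54 two-sided.

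**Step 5: power with baseline as covariate.** Taking 44.43 as the week-2 SD, the residual SD is 44.43 × √(1 − r²), which cannot exceed 44.43. F-test power is 90% at r = 0, 91% at 0.2, 93% at 0.3, 95% at 0.4 and 97% at 0.5. The one degree of freedom spent on the covariate does not alter these figures.

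**The case against.** The best defence is that the inputs in 2.9 agree with one another. The mean, the SD and the 30 μmol/l difference are all worded as levels, and the printed arithmetic reproduces exactly. Under randomisation the expected group difference in week-2 level equals that in change, so 30 serves for either. On this view one sentence carries the wrong label. This stands as far as it goes: there is no arithmetic error. It does not remove the mismatch, because 2.6 also names a change, and the analysis in 2.10, read as its group-by-time test, assesses the raw change without baseline adjustment.

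Two stronger readings are tempting, and the document supports neither.

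- A reader might infer that the 90% holds only if r is exactly 0.5. It does not: 0.5 is a lower threshold, and power exceeds 90% above it. The value itself rests on equal SDs and the omnibus F test (step 4).
- A reader might infer that the trial is underpowered, because patients enter during an acute rise and recover unevenly, which would lower r. Nothing in the article quantifies this. Eligibility across CKD stages 2–4, GFR 15 to 89 in Table 2, argues the other way, since a wide and lasting spread between patients raises r.

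Nor is this merely detail that a journal article leaves to the full protocol. The article does give a variance input, but attaches it to a different quantity from the outcome it names.

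**Conclusion.** The concern holds in limited form. The stated 90% is not established for the change outcome. It is supported only if r is about 0.5 or higher, given equal SDs at the two visits, 43 evaluable per group and the omnibus F test. Across assumed r from 0.2 to 0.7, power runs from 72% to 99%, and the total needed for 90% runs from 255 down to 102, against 162 planned. The document does not show on which side of the threshold the trial lies. What the earlier studies cited in 2.9 report on the SD of change cannot be checked here.

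This is a mismatch between the sized quantity and the named outcome that should be corrected. It is not evidence that the trial is too small. The one-sided α in 2.9 against two-sided testing in 2.10 is a separate matter.

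**What to change.** Make 2.6, 2.9 and 2.10 use the same quantity.

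- **Preferred:** define the primary comparison as week-2 creatinine between groups with baseline creatinine as covariate, and name that ANCOVA in 2.10 in place of the repeated-measures ANOVA. The SD of 44.43 is then an upper bound on the residual SD, and omnibus F-test power is at least 90% at any r. The text should limit that assurance to the F test. The hypothesis in 2.9 is that the combination beats both other groups, and the F test does not show that. With 43 per group and two-sided pairwise t tests at 0.05, the chance of winning both comparisons is about 79% at r = 0 and about 91% at r = 0.5 with adjustment.
- **Alternative:** keep the raw change, replace 44.43 by the SD of the 2-week change from the same earlier studies, and restate the power for 43 evaluable per group.

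**Cost:** wording in 2.6, 2.9, 2.10 and the abstract. Creatinine is already measured at both visits, so neither option adds visits or, at the planned size, patients. If the raw change is kept, the restated power may be less favourable than 90%.

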### 2.4. Randomization and Blinding

A simple random method is adopted, and SPSS (version 21.0) software will be used by independent biostatisticians to generate random number sequences. Written informed consent should be signed immediately by himself/herself, agreeing to voluntarily enroll in the trial. Participants should be consented for randomization and participation. According to the sequence of enrolling in clinical observation, participants will be randomly numbered and divided into the RG group, the CHF group, and the RG + CHF group by investigators at 1 : 1 : 1 ratio. During randomization producer, sealed envelopes marked with sequential coding numbers will be adopted to keep allocation details, and group allocation should be kept blind to patients, biostatisticians, and investigators. As placebo is not used in the control group, it is not possible to be blind in the treatment. However, it is masked from staff performing all laboratory investigations.

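### The sample size is labelled one-sided but the analysis is two-sided, and the 90% power belongs to a three-group F-test, not to the hypothesis that RG + CHF beats each of the other arms

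*Protocol article*

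**What the plan says.** Section 2.9 (Sample Size Estimation) bases the sample size on change in serum creatinine (Scr) from baseline. It states that "the mean value of Scr was 160.39" µmol/l and that "the standard deviation was 44.43" µmol/l. The hypothesis is that Scr in the RG + CHF group "would be significantly lower than the other two groups by more than 30" µmol/l. Power is given as "0.90 and significant difference" as "0.05 (one-sided test". The sentence on loss and size follows directly: "one-sided test). Considering 20% drop rate, the estimated sample size for randomization will be 54 cases in each group", which makes 162 in total. PASS is named as the software, but not the test or procedure used in it.

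Section 2.4 has patients "divided into the RG group, the CHF group, and the RG + CHF group by investigators at 1 : 1 : 1 ratio".

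Section 2.10 (Statistical Analysis) tests Scr by one-way ANOVA with repeated measures and adds: "Two-sided tests will be used for all statistical tests", with significance at P < 0.05. It assigns Student's t-tests to the secondary outcomes. Section 2.6 (Outcome Measures) names the primary outcome as the change in the slope of Scr over 2 weeks.

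**The concern.** Three things do not fit together.

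- **Sidedness.** The same 0.05 is one-sided in the sizing paragraph and two-sided in the analysis section. Neither section qualifies the other. A favourable result with a two-sided p between 0.05 and 0.10 would meet one rule and fail the other.
- **What the 90% refers to.** The hypothesis makes two directed claims: the combination is lower than RG, and lower than CHF. A calculation for an overall three-group difference does not give the power for either claim, or for both together.
- **The SD.** The mean and SD quoted are those of an Scr level, while the outcome is a change or slope. The variance of a change also depends on the baseline to week-2 correlation, which the article does not give.

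At stake is whether a reader can tell what error rate and what power the trial was designed to have for the claim it wants to make.

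**Working it through.** **Inputs (section 2.9 unless noted).** Difference δ = 30; SD σ = 44.43; alpha 0.05; power 0.90; loss 20%; three equal groups (section 2.4). Group means are taken as 160.39, 160.39 and 130.39, the last being 160.39 − 30.

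**1. Reproducing 54.** For a one-way ANOVA F-test, the grand mean is 150.39 and the deviations are +10, +10 and −20, so their squares sum to 100 + 100 + 400 = 600. The noncentrality is λ = n × 600 / 44.43².

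- n = 42: λ = 12.77, power 0.895.
- n = 43: λ = 13.07, on 2 and 126 df, critical F = 3.068, power 0.9025.

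So 43 evaluable per arm are needed, and 43/0.8 = 53.75, rounded up to 54. This matches the article exactly.

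**2. Two-group t-tests on the same inputs.** The noncentrality is δ / (σ√(2/n)) on 2n − 2 df.

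| Test | Evaluable per arm for 90% | Power reached | After 20% loss |
|---|---|---|---|
| One-sided 0.05 | 39 | 0.905 | 39/0.8 = 48.75, so 49 |
| Two-sided 0.05 | 48 | 0.906 | 48/0.8 = 60 |

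Neither gives 54. The one-sided label therefore does not describe the calculation that matches the figure. The F-test uses only its upper tail but has no direction, which may explain the label. That is an inference, because section 2.9 names no test.

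**3. Power for the stated hypothesis.** Evaluable per arm: 54 × 0.8 = 43.2, taken as 43. The noncentrality is 30 / (44.43 × √(2/43)) = 3.131.

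- Each comparison, two-sided 0.05 (critical t = 1.989 on 84 df): power 0.872.
- Each comparison, one-sided 0.05 (critical t = 1.663): power 0.928.
- Both comparisons significant, two-sided 0.05 each, no adjustment: about 0.79 by simulation with normal data (0.790 with each pair's own variance, 0.795 with variance pooled over three groups). As a check, two independent tests would give 0.872² = 0.76. Sharing the RG + CHF arm makes the two tests positively correlated, which raises the figure.

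**4. Level against change.** If the SD is 44.43 at both visits and the correlation is r (assumption), the SD of the change is 44.43 × √(2(1 − r)). Power per two-sided comparison with 43 per arm:

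| r (assumed) | SD of change | Power |
|---|---|---|
| 0.3 | 52.57 | 74% |
| 0.5 | 44.43 | 87% |
| 0.7 | 34.42 | 98% |

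At r = 0.5 the change has the same SD as the level, so step 3 carries over to a change score only near that value. The F-test power in step 1 shifts with r in the same way. Table 3 schedules Scr at baseline and week 2 only; on that schedule a slope is the change divided by two weeks, so the same correlation decides the matter.

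**The case against.** The best defence is that the number is right. This is a three-arm trial, section 2.9 names no two-sample test, and the F-test that yields 54 is in the same family as the Scr analysis in section 2.10. That stands, and it rules out several stronger readings that a reader might infer.

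- **That 54 is an arithmetic error.** It is not. Difference, SD, alpha, power and loss give 54 exactly under a three-group F-test. Only the one-sided label fails to fit.
- **That the planned analysis needs 60 per arm, 180 in all.** That is the size for 90% on a single two-sided t-test. Section 2.10 names no pairwise t-test for Scr, so it is not the stated analysis.
- **That the 90% is wrong for the test to be run.** Section 2.10 names an ANOVA, and the omnibus F-test has about 90% power at 43 per arm, given the SD. The gap is between that test and the hypothesis in section 2.9.
- **That the plan permits a one-sided p-value.** Section 2.10 sets two-sided tests throughout, and the one-sided phrase occurs only in the sizing paragraph. The conflict should be removed, but the analysis section is clear.
- **That a shortfall below 90% is established for the real endpoint.** It is not. Over the assumed correlations, power per comparison runs from 74% to 98%. An ANCOVA at r = 0.5 would give about 95%, but that rests on one assumed value and on an analysis the article does not name.

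The defence does not remove the contradiction on sidedness, and it does not make omnibus power answer the pairwise hypothesis. A significant F-test does not show that the combination is lower than either other arm, let alone both.

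**Conclusion.** The point holds as a mismatch of labels and claims; the total of 162 is not in error. Sections 2.9 and 2.10 contradict each other on sidedness. The 54 per arm matches a three-group ANOVA F-test with 90% omnibus power.

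For the hypothesis actually written, the figures at 43 evaluable per arm are about 87% for each two-sided comparison and about 79–80% for both, against the stated 90%. These rest on equal means of 160.39 in the two single-treatment arms, a common SD of 44.43, exactly 20% loss and no multiplicity adjustment. For a change score they also need a baseline to week-2 correlation near 0.5, which the article does not support or contradict.

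**What to change.** Keep N = 162 and amend section 2.9 as follows.

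1. Delete the one-sided label, so that the section agrees with section 2.10.
2. Name the calculation: three-group one-way ANOVA F-test, alpha 0.05, means 160.39, 160.39 and 130.39, SD 44.43, 43 evaluable per arm, 90% omnibus power, 54 per arm after 20% loss. The sponsor should confirm this against the PASS output, since the test is inferred from the match.
3. State the power for the hypothesis: about 87% for each two-sided 0.05 comparison of RG + CHF with another arm, and about 79% for both being significant.
4. Say that 44.43 is the SD of an Scr level, and give the SD or correlation assumed for the change, with the range of power that follows (74% at 0.3, 87% at 0.5, 98% at 0.7).

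The cost is a few sentences and a slightly less favourable power statement. No extra patients are needed and the conduct of the trial does not change. The amendment should be made before the data are analysed, so that the error rate for the primary test is settled beforehand.
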